#### Objective #1

The primary objective is to determine if the PCCI results in improved patient quality of life (communication and psychosocial domains) and satisfaction with care. The outcomes at each time point will be analyzed as repeated measures data using hierarchical regression methods to account for the nesting within the data. The patient outcomes at each time point will be measured for a specific patient by a specific staff member. The two levels of the model are expected to include (Level 1) repeated measures nested within (Level 2) patients. An appropriate model is expected to include Level 2 predictors, such as severity of patient impairment, as covariates and the effect of PCCI as the fixed effect of most interest. Because the PCCI will be specifically tailored to account for characteristics of the communication challenges of each individual patient, Level 2 predictors are expected to be an important part of the model. Characteristics of staff will be incorporated into the model by treating staff as a crossed random effect. The steps of building the model will be to 1) estimate the parametric structure of the covariance matrices; 2) model the structure of the mean responses by specifying the fixed effects; 3) specify the covariance structure within and among patients and staff; and 4) fit the mean model, accounting for the covariance structure. This will be repeated until an appropriate and parsimonious model is built. The results of most interest are the set of planned post-hoc contrasts that will identify the point in time when changes in the outcome occurred and whether the change in the outcome was maintained over time, increased with additional exposure to the improved patient-staff communication, or deteriorated over time. The expectations are that changes in the outcomes will occur at the first post-intervention time point and will be maintained throughout all subsequent time points. The analysis will be performed separately for each outcome measure.

#### Objective #2

The second objective evaluates the effects of the PCCI on staff’s attitudes and knowledge about caring for patients with communication impairments due to stroke. The same approach to analysis will be used to assess the effects of the PCCI on staff experiences as was used to assess the effects of the PCCI on patient quality of life. Staff attitudes and knowledge of care are now the outcomes measured at each time point and will be analyzed as (Level 1) repeated measures nested within (Level 2) patients using the hierarchical regression methods described in the previous paragraph.

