**Methods/design:**

A quasi-experimental repeated measures non-equivalent control group design in a complex continuing care facility is being used. Patients with a communication impairment post-stroke admitted to the facility are eligible to participate. All staff nurses are eligible. Baseline data are collected from staff and patients. Follow-up will occur at 1 and 3 months post-intervention. Subject recruitment and data collection from 60 patients and 30 staff will take approximately 36 months. The Patient-Centred Communication Intervention consists of three components: (1) development of an individualized patient communication care plan; (2) a one-day workshop focused on communication and behavioural management strategies for nursing staff; and (3) a staff support system. The intervention takes comprehensive patient assessments into account to inform the development of communication and behavioural strategies specifically tailored to each patient.

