#### Nursing staff measures

##### Nursing staff characteristics

The following data are obtained from the nursing staff by the RA following a nurse-patient observation. Characteristics include age, sex, education level, job status, job category, and length of time employed on the unit. The job category of the staff will be used as a co-variate when analyzing staff outcomes, as staff’s knowledge of communicating with patients with communication impairments differs depending on job category [45]. Most staff members are willing to participate because of the endorsement of our research by administrators at the institution and based on previous recruitment rates for evaluation studies [26,45]. A sample size of 19 staff was sufficient to demonstrate changes in staff’s attitudes in the pilot study.

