#### Nursing staff outcomes

1. Attitudes of the nursing staff toward communicating with patients with communication impairment are measured with the Communication-Impairment Questionnaire (CIQ), an 8-item self-report scale [24]. The measure focuses on the extent to which a staff member espouses a person-centred approach in relating to individuals with communication impairments. Reliability data from the pilot study indicated a Cronbach’s alpha coefficient of .73. In addition, the scale was sensitive to change following communication interventions [24,26].

2. Knowledge of staff working with patients with communication disabilities is measured using the Providers Interactional Comfort Survey (PICS)[20]. The scale has an acceptable reliability with a Cronbach’s alpha coefficient of .81 and has shown sensitivity to a communication intervention [45]. The measure focuses on nurses’ perception of their competence, confidence, willingness, frequency, and scope of practice related to interacting with patients.

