### Trial status

The trial is now accruing during the intervention phase of the study. Progress to date includes the collection of data on all 30 control subjects; 16 intervention participants are enrolled with an end date of March 2013. Twenty-five staff nurses have agreed to participate in the study and have completed questionnaires.

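### Objective #2 names patients as the Level 2 unit for nurse self-report scores; the unit should be the nurse, and the standard errors depend on a staff term the paragraph does not restate

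*Protocol article*

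**What the plan says.** Under Objective #2 the protocol article states that "The same approach to analysis will be used to assess the effects of the PCCI on staff experiences" as for patient quality of life. It then says that staff attitudes and knowledge "will be analyzed as (Level 1) repeated measures nested within (Level 2) patients using the hierarchical regression methods described in the previous paragraph".

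The paragraph it points to, Objective #1, sets out two levels (occasions within patients) and adds: "Characteristics of staff will be incorporated into the model by treating staff as a crossed random effect". One of its model-building steps is to "specify the covariance structure within and among patients and staff".

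The staff outcomes are described under Nursing staff outcomes: "Attitudes of the nursing staff toward communicating with patients with communication impairment are measured with the Communication-Impairment Questionnaire (CIQ), an 8-item self-report scale". The PICS likewise records nurses' perceptions of their own competence and confidence. Under Nursing staff characteristics the article adds: "The job category of the staff will be used as a co-variate when analyzing staff outcomes".

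On numbers, the abstract says "Subject recruitment and data collection from 60 patients and 30 staff will take approximately 36 months", and Trial status reports: "Twenty-five staff nurses have agreed to participate in the study and have completed questionnaires". The Sample size section recruits nurse-patient dyads, 30 patients per cohort, and names the CIQ as the primary staff outcome.

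**The concern.** A CIQ or PICS score is a property of the nurse who fills it in. With 60 patients and 25 to 30 nurses there are on average 60/30 = 2 to 60/25 = 2.4 patients per nurse. One nurse's scores can therefore sit under two or more Level 2 units that a patient-only hierarchy treats as independent. The wording looks carried over from Objective 1 with only the outcome changed.

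At stake is the inference on the staff primary outcome. An analyst could fit patients alone or patients with staff crossed, and both would claim to follow the paragraph. The two models give different standard errors. A second risk is separate from the choice of random effects: if a nurse completes the CIQ once per occasion and that score is entered for each of her patients, the data set contains copies that look like new observations.

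**Working it through.** **1. The plan's own figure.** Inputs from Sample size: improvement 2.4, SD 4.1, 80% power, alpha 0.05 (taken as two-sided), correlation 0.40 among three repeated measures. A two-group normal approximation with the factor (1 + 2 × 0.40)/3 = 0.60 gives

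N = 4 × [(1.960 + 0.842)/(2.4/4.1)]² × 0.60 = 54.97, so 55 as stated.

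The same formula with effect size 0.76 and 90% power gives 43.66, so 44, the stated patient figure. The staff calculation thus compares two groups averaged over three occasions and treats 55 units as independent.

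**2. Cohort comparison with the staff term left out.** The documents give no staff variance component and do not say which nurses serve which cohort. Assumptions:
- 60 dyads, 30 per cohort, 30 nurses with 2 patients each, 3 occasions.
- Total variance 1 and residual 0.6. The remaining 0.40 is split into staff variance s and patient variance p = 0.40 − s, with s from 0.2 to 0.4.

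The patient-only model reports SE = √[2 × (0.40 + 0.6/3)/30] = √0.040 = 0.200.

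*Each nurse in one cohort (15 per cohort):* true SE = √[2 × (s/15 + p/30 + 0.2/30)].
- s = 0.2: √0.0533 = 0.231. The reported SE is 1 − 0.200/0.231 = 13% too small. Type I error 2[1 − Φ(1.96 × 0.200/0.231)] = 9%.
- s = 0.4: √0.0667 = 0.258. The reported SE is 23% too small. Type I error 13%.

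*Each nurse in both cohorts:* the staff effect cancels, and true SE = √[2 × (p + 0.2)/30].
- s = 0.2: 0.163. The reported SE is too large; type I error 1.6%.
- s = 0.4: about 0.116. The reported SE is too large; type I error 0.1%.

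Methods/design gives only two staff occasions. Replacing 0.6/3 by 0.6/2 changes the one-cohort result to 12% to 20% too small, with type I error 8% to 12%. The conclusion is the same.

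**3. The same comparison with staff as a crossed random effect.** With the correct variance components, the model SE equals the true SE in both layouts.

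**4. Time contrast when scores are copied.** Suppose one nurse score per occasion is entered under two dyads (an assumption, since the documents do not say how scores are recorded). With residual variance σ², the change between two occasions has true variance 2σ²/30, from 30 distinct scores per occasion. A model with 60 dyads reports 2σ²/60 if it estimates σ² correctly. The SE is then too small by a factor √2, and type I error is 2[1 − Φ(1.96/√2)] = 17%.

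If the patient variance is estimated as zero, the copies also pull the residual down. With two occasions each nurse contributes an expected within-nurse sum of squares of 2σ² on 3 degrees of freedom, so the estimate is 2σ²/3. The variance is then understated threefold, and type I error is 2[1 − Φ(1.96/√3)] = 26%. A crossed nurse intercept removes neither problem, because it captures stable differences between nurses and not a residual shared on one occasion.

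**The case against.** The strongest reply is that Objective #2 does not stand alone. It adopts the Objective #1 methods by reference, and those include staff as a crossed random effect and a covariance structure for both patients and staff. Objective #1 itself names only two levels before adding staff, so repeating the level wording does not show that staff was removed. This stands. A reader might infer that patients are the only grouping unit, and hence that the Objective 2 standard errors are wrong in any event. The documents support neither inference.

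A reader might also infer that job category has no place in a model with patients at Level 2. That fails too: a staff covariate can be a fixed effect whatever unit carries the Level 2 label.

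The sizes are open to challenge as well. The 0.40 is the correlation among repeated measures, not between different patients' records for one nurse, and overlap of nurses across cohorts is not settled. That is why a range and both directions are given.

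What the reply leaves untouched is that the named unit does not fit the outcome. The imported term was introduced to bring staff characteristics into a patient-outcome model, and Objective #1 lets the model be rebuilt until it is parsimonious, so nothing secures the term. Nor does keeping it deal with copied scores.

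**Conclusion.** The point holds in a conditional form. Patients are the wrong Level 2 unit for the CIQ and PICS, and this is a statement in the plan rather than detail left to a later document.

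If the crossed staff effect is not kept, the SE of the cohort comparison is about 13% to 23% too small (type I error about 9% to 13%) when each nurse serves one cohort, and too large when nurses serve both. These figures rest on two patients per nurse, three occasions, and half to all of the 0.40 being due to staff. They concern the cohort difference averaged over occasions, the contrast that reproduces 55. A stable nurse effect cancels from a change within a dyad.

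If the staff effect is kept, the cohort comparison is sound on this ground. The time contrast is still too precise (type I error about 17% to 26% under the assumptions in step 4) if a nurse's score is copied across dyads on the same occasion.

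A reader might go further and conclude that Objective 2 should become a within-nurse comparison of scores before and after the workshop. The documents do not support that: the design has a control group, and the staff sample size reproduces as a two-group calculation. Correcting the unit does not require changing what is estimated.

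**What to change.** Rewrite the Objective #2 paragraph before analysis so that it states:
- Level 1 is the repeated CIQ or PICS score, and Level 2 is the nurse, with a random intercept.
- There is one record per nurse per occasion, not one per dyad.
- Job category is a nurse-level fixed effect.
- Patient is added as a crossed random effect only if the scores are collected separately for each patient.
- The PCCI effect and the control-versus-intervention comparison stay as planned.
- Each staff record is marked as before or after the workshop. Staff were trained once the controls were accrued, and staff follow-up is timed by the patient's stay, so a baseline taken with an intervention patient may fall after training.

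The cost is one paragraph of wording plus a nurse identifier and a workshop flag on each staff record. No new data are needed.

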#### Treatment fidelity

Descriptive statistics will be used to examine the frequency of the adherence to the treatment fidelity at the post-test data collection periods. A total score will be computed to quantify the number of specific communication strategies that are actually implemented for each patient at each occasion of measurement. The relationship between the number of strategies applied and patient outcomes at post-test at time 1 will be examined. This as treated analysis will supplement the intention-to-treat analysis in determining the effectiveness of the intervention. In the hierarchical model, this total score of treatment fidelity can be included as a Level 2 predictor.

## Discussion

This study will lead to the improvement of services provided to care for stroke patients living in CCC by enhancing communication between nursing staff and patients with communication impairment in everyday practice. Patient-centred care involves staff communicating effectively to understand patients’ needs, thus enhancing their well being and maintenance of autonomy. The PCCI also has the potential to reduce nursing staff burnout and reduce turnover in facilities. By improving communication, patients will become less agitated and caregiver interactions less stressful. The findings will serve as the basis for establishing guidelines for best practices in institutional settings. Study findings will have relevance for managers and policy makers because they will inform nursing and speech language pathology services for patients with communication difficulties in institutional care, which are transferable to other health jurisdictions.

Implementation of the PCCI is timely. This study is implementing the PCCI in CCC with the objective to educate, train and support nursing staff in communicating effectively with patients who have communication impairments as a result of a stroke. The significance of this research is that the PCCI will provide nursing staff with viable strategies to communicate effectively with patients post-stroke. When interactions are effective and patients’ needs are met, patients will be less agitated, and their quality of life will be optimized. Because agitation can create an inordinate burden on staff, its reduction has the additional significance of reducing the stress of nursing staff. Our research aims to improve the quality of life and health of older persons by understanding how to provide more effective health services to institutionalized elders.

### Trial status

The trial is now accruing during the intervention phase of the study. Progress to date includes the collection of data on all 30 control subjects; 16 intervention participants are enrolled with an end date of March 2013. Twenty-five staff nurses have agreed to participate in the study and have completed questionnaires.

## Abbreviations

CCC: Complex Continuing Care; LTC: Long-Term Care; MECQ-LTC: Montreal Evaluation of Communication Questionnaire for Use in Long Term Care; PCCI: Patient-Centred Communication Intervention; SAQOL: Stroke and Aphasia Quality of Life; SLP: Speech Language Pathologist.
